## Abstract

It is known that the presence of orthodontic brackets predisposes for a change in the biofilm, facilitating the development of gingivits. The sites are difficult to access with a toothbrush and periodontal curette, worsening inflammation, in addition, a gingival hyperplasia is associated with poor hygiene. The objective of this study is to evaluate the impact of photodinamyc therapy (PDT) as an adjuvant treatment, considering clinical immunoregulatory and microbiological parameters. This randomized, controlled, double-blind clinical study will include 34 patients, both genders, having used fixed appliance for more than 12 months, with gingivitis. Participants will be divided into two groups: G1 (n = 17)- Scaling and Root Planing + PDT placebo and G2 (n = 17)- Scaling and Root Planing + PDT. In G2 the following dosimetric parameters will be used: methylene blue 0.005%, λ= 660 nanometers (nm), 9 Joules (J) per site, irradiance= 3.5Watts (W)/ centimeters (cm), radiant exposure= 318J/cm^2^. All participants will receive oral hygiene guidance prior the curetes scaling. The clinical periodontal data to be analyzed are plaque index, gingival index and probing depth. Crevicular fluid, from 4 pre-determined sites and saliva, will be collected and analysed for IL-6, IL-1β, IL-8, TNF-α and IL-10 cytokines using ELISA (Enzyme immunoabsorption assay) method. Total *Bacteria* count will also be performed, by qPCR and *Universal16SrRNA* gene. All analysis will be realized using in the baseline (T_0_), 7 (T_1_) and 21 (T_2_) days after treatment. Oral health-related quality of life will be assessed using the OHIP-14 questionnaire at times T_0_ and T_2_. If sample distribution is normal, the Student T-test will be applied if it is not normal, the Mann-Whitney test will be used. The data will be presented in terms of ± PD and The significance level will be set at p < 0.05. Our results may improve quality of life and add data to establish a therapeutic alternative for gingivitis during the orthodontic treatment. Registration: clinicaltrials.gov NCT04037709. https://clinicaltrials.gov/ct2/show/NCT04037709 - Registered in July 2019.

## Introduction

1

It is known that the presence of fixed orthodontic devices - brackets, bands and orthodontic elastics, facilitate the biofilm accumulation due to the difficulty in properly brushing, besides favoring the change in the quantity and quality of biofilm.^[1,2,3]^ Retentive areas such as brackets are favorable for microbiological aggregation and thus for the inflammatory process in local tissues.^[4,5]^

Biofilm accumulation occurs in brackets of various materials, such as stainless steel, gold, ceramic and plastic,^[6]^ whether conventional or self-bonding.^[7]^ For Jurela A, et al, 2013^[8]^ there was no difference comparing microorganisms in saliva of users of brackets composed of different materials, for Pandis N, et al, 2010^[7]^ there was also no difference in microorganisms in saliva with two different types of devices: conventional and self-ligating. Regarding gum health, ceramic brackets appear to have better results, especially for adolescent patients, which correspond to most users of multi-brace orthodontics.^[9]^ Microbiological adhesion to brackets is a predisposing factor to development of gingivitis and it increases the retentive surface. Inflammatory changes are frequently observed in the presence of non-removable orthodontic devices in patients with dentomaxillary anomalies. These parameters can be clinically and chemically evaluated, Bracket placement was followed by deterioration in oral hygiene, increased total protein levels, hydrogen sulfide and nitrogen metabolites in oral fluid.^[3]^ Microscopic analysis demonstrates the direct effect of bracket bonding on the middle third of the buccal surface of the tooth crown, where the bonding area even after bracket removal has numerous areas of disordered grooves and fissures, which may facilitate the retention of microorganisms. These areas are very different from the smooth surface of the lingual faces, for example, which do not receive any type of bonding material. Therefore, caution in bonding is required to avoid overeating as well as clinical alternatives in fixed fixture removal and proper polishing procedures.^[10]^

Oral hygiene is one of the most important questions for patients in orthodontic care, since the presence of fixed devices (brackets and bands) and removable devices (wires and elastics) decreases the efficiency of tooth brushing, especially in the interproximal areas, causing high measurements in the plaque index (PI) and gingival index (GI).^[11]^

Biofilm accumulation is better controlled in those patients who have the habit of brushing their teeth two or more times a day, using interdental brushes, flossing and having frequent consultations in a short time. The rate of PI and gingival bleeding in patients who control oral hygiene during orthodontic treatment is significantly lower. To maintain gum health and reduce the amount of biofilm adhered to orthodontic appliances, patients should be constantly informed about the merits of oral hygiene brushing.^[11,12]^

Periodontal health is defined by the absence of clinically detectable inflammation. Gingival homeostasis can be recovered in individuals who have already had gingivitis and the fact that there is no bone tissue involvement facilitates the return to the pre-pathogenic condition.^[13]^ Clinically, the healthy periodontium is characterized by the absence of bleeding, erythema and edema, physiological with bone levels range from 1.0 to 3.0 mm apical to the enamel-cement junction (ECJ) line. In the transition from periodontal health to gingivitis, ≥10% of bleeding sites and clinical probing depth greater than 3.0 mm can be observed. However, this probing depth greater are gingival hyperplasia, a condition where the increase in gingival tissue above the ECJ line forms a deeper pocket, unlike periodontitis, where the increase in clinical probing depth occurs due to bone loss below the ECJ line. In cases of gingival hyperplasia there is also a possibility of recovering the health and appearance of the gum, because if the regression is not spontaneous, surgical removal may be used.^[13]^ For clinical diagnosis, the gingival bleeding rate is a relevant parameter, where a tube exerts slight pressure on the gingival margins and bleeding can occur immediately or within seconds.^[14]^

Gingivitis can be classified as biofilm-induced or non-biofilm-induced. Those biofilm-induced may be: a) associated with dental biofilm only, b) mediated by local and systemic risk factors or c) drug-influenced gingival enlargement.^[15]^ Those non-biofilm-induced is caused by systemic factors, regardless of the presence of biofilm, such as genetic, hormonal, immune factors, among others.^[16]^ From a microbiological point of view, we have the contemporary model of host - microorganism interaction in the pathogenesis of periodontitis, where the host response drives an incipient dysbiosis (gingivitis). If the biofilm is not interrupted/removed, blunt dysbiosis results and perpetuates chronic and destructive inflammation. In the presence of incipient dysbiosis, the host may produce, polymorphonuclear neutrophils, T and B defense cells, antibodies and with the progression of inflammation due to the high amount of biofilm there is also production of antigens, perpetuation of microorganisms with high virulence and lipopolysaccharides.^[13]^ Thus, biofilm is considered a determining factor for gingival inflammation and its severity depends on local and systemic factors.^[15]^

Some periodontopathogens are well known to be present in the destruction of periodontal tissues, such as *Aggregatibacter actinomycetemcomitans*, *Porphyromonas gingivalis* and *Fusobacteria nucleatum*. The *Prevotella intermedia* was also correlated as an anaerobic bacterium present in biofilm samples from patients using fixed orthodontic appliance.^[17]^ However, emerging evidence suggests a clustering of bacteria rather than individual species. Actually, the diagnosis through biological markers have been considered more robust in discriminating bacterial functions such as proteolysis, flagella and bacterial motility. There is the characterization of the disease and not of a species, so the presence of a spare species is not considered a pathognomonic sign.^[14]^

Currently biomarkers have also been used in the diagnosis of gingivitis. Inflammatory cytokines from crevicular fluid and saliva have been evaluated by ELISA^[18]^ real time polymerase chain reaction (PCR) method^[19]^ For the treatment of gingivitis, the gold standard is usually biofilm scraping, usually performed with gracey curettes and/or ultrasonic equipment.^[20]^

The major drawback in treating gingivitis with conventional methods in the patient with brackets and bands is that there may be gingival hyperplasia covering the upper base toward the cervical and upper fins, ideally to perform instrumentation around the entire bracket until the amelocemental line, considering the potential for biofilm accumulation. Comparing the angles of piezoelectric ultrasound in biofilm removal brackets was performed around bracket only at the occlusal base and it was shown that a prolonged ultrasonic instrumentation should not be performed at the bracket base, due to the possibility of detachment^[20]^

Mechanical removal of gold standard biofilm in the treatment of periodontal diseases is impaired in hard to reach areas because of the difficulty in entering small areas. The Photodynamic Therapy (PDT) has been shown to be promising as adjunctive therapy to periodontal treatments with regard to its antimicrobial action, the technique consists of the use of low wavelength lasers associated with a photosensitizing agent.^[22]^ PDT has no bacterial selectivity and side effects such as bactericidal/ bacteriostatic, preserves the oral microbiota and has no anti-inflammatory toxicity.^[23]^ There is a triad for PDT to happen: photosensitizing agent, light and oxygen.^[24]^ Photosensitizing agent has the property of selective accumulation in both normal and infected tissues, it is able to penetrate damaged and dead tissues without developing selectivity.^[25]^ The photosensitizing agent is composed of cationic molecules that have low molecular weight, when inserted in a pouch has the ability to quickly bind to local bacteria.^[26]^ Methylene blue (MB) is the most widely used^[27,28]^ in Brazil, being the only one that has ANVISA approval. To provide the antimicrobial effect, the dye is associated with a light (low power laser), establishing a photochemical effect, which occurs due to the presence of molecules sensitive to certain wavelengths. There is a photoregulation, changing the functional and metabolic activity of the irradiated cell.^[29]^ MB has wavelength absorption from 600 to 660 nm, being the appropriate spectrum for the therapeutic window.^[30]^ The therapeutic window of PDT is effective in eradicating colonies or biofilm and may intensify the results of conventional mechanical treatment.^[25,31]^ The oxygen molecules of the Photosensitizing when they excited by light irradiation, originate reactive oxygen species, such as singlet oxygen, which is capable of causing selective bacterial death.^[26]^ Oxygen is the third element of the fundamental triad in PDT. The joint use of periodontal treatment and PDT has been considered in reducing the extent of inflammatory gum signs. To evaluate laser effectiveness in this context, it is important to consider a placebo group, making the study blind. Furthermore, the experimental hypothesis is aimed at assessing whether PDT associated with periodontal treatment is effective in the treatment of gingivitis (gingival hyperplasia) caused by poor hygiene associated with orthodontic braces in healthy young patients.

## Materials and methods

2

This is a single-center randomized, double-blind, prospective, controlled trial with 21 days of follow-up. A revised version of the manuscript has been submitted, and SPIRIT-Checklist and SPIRIT-Figure. The project was submitted to the Research Ethics Committee (REC) of the Universidade Nove de Julho – UNINOVE and approved (#3505689). After verbal and written explanation of the study, participants who agree to participate in the study will sign an Informed Consent Form (ICF) and a Terms of Assent (TA) for children between 10–18 years of age, the person responsible for applying the therm will be the researcher ([name]). The study will be conducted in accordance with the *Declaration of Helsinki* (revised in Fortaleza, 2013). The Project was registered at www.clinicaltrial.gov (NCT 04037709). The patients will come from three centers located in Brazil: Dellê Dentistry – [name]; Odontocorpus Dentistry and Health – [name]; and [name] and Team Clinic– [name], from July 2019 to December 2021. There is no conflict of interest regarding the clinics where the research will be conducted. Project receive grant from Brazilian National Coordination for the Improvement of Higher Education Personnel CAPES # 1690040 (CAPES Portuguese: Coordenação de Aperfeiçoamento de Pessoal de Nível Superior (CAPES). Any intercurrence will be notified to the REC and reported in the publication. If necessary, the study will be ended before the stated date. In addition, if evaluations of the dosimetric parameters for the laser, as described in the initial protocol, show that the results are not adequate, the protocol may be adjusted. The sample will be composed of patients who have used a fixed appliance for at least 12 months and with gingivitis present, detailed description in the sample. The experimental design will consist of 2 groups (described in detail in Experimental Design). Samples will be collected for microbiological evaluation and measurement of inflammatory cytokines in the crevicular fluid and saliva. Periodontal clinical data will be collected for diagnosis of gingivitis and for comparison of these parameters after 7 and 21 days to check for improvements. The Oral Health Impact Profile Questionnaire (OHIP-14) questionnaire will also be applied to measure the quality of life related to oral health.

All data will be published without any type of restriction and will be made available. If participants wish to receive the research data they can give their e-mail and a copy of the article will be sent to them as soon as it is published. Furthermore, all data collected will be kept confidential.

### Calculation of sample size

2.1

To achieve an effect size = 0.40 between two groups (conventional treatment and PDT), for the difference in the amount of bacteria present in the crevicular fluid of participantstreated with scaling and those treated with PDT, assuming a type 1 error of 0.2^[1]^ and 95% confidence level, the total sample size will be 34 participantsdistributed into 2 groups. The sample calculation was performed in Excel, based on the calculation formula described by Kadam and Bhalerao. Considering a 20% drop-out, 3 extra participantswill be inserted into each group, if there is said drop-out this will provide a final sample of participants per group.^[32]^

To ensure participants’ adherence to the research, the steps will preferably coincide with the participants's return visits to their routine orthodontic appliance maintenance. Participants uptake will occur during routine consultations with the orthodontist.

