### Statistical analysis

2.15

Statistical analysis will be performed using only the data obtained from patients who have completed the study. If the sample is normally distributed, Student's T test will be used to compare the means of the continuous and dependent variables. If the distribution is not normal, the Mann-Whitney test will be used. Data will be presented by their means ± SD and the p value will be set at 0.05. All tests will be performed using GraphPad Prism 5 (GraphPad Software, San Diego, USA). The significance level will be set at *p* < 0.05.

Spreadsheets with the survey data will be stored in their own space during the survey. To avoid duplicate data entry, only one researcher will be responsible for entering the data into the spreadsheets for further statistical analysis. The responsible is [name].

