The gingival index (GI) will be applied according to the dichotomous score,^[34]^ which is presented as a percentage, but it will be considered gingivitis if more than 10% of the sites present bleeding, in accordance with Chapple, 2018.^[13]^ The GI was defined for this study as a primary variable, since its introduction has been widely used in periodontal clinical research and represents the most used index for gingival inflammation in clinical trials with preventive and therapeutic strategies,^[14]^ providing a basis for comparisons between studies.

As biofilm is basically composed of bacteria and your quantity determines the presence of gingivitis, we seek to characterize the disease and not if there is an extra species of microorganism, following Trombelli, 2018,^[14]^ who states that a prominent species is not a pathognomonic sign of gingivitis. Therefore, microbiological analysis of the crevicular fluid and saliva will be performed via universal gene 16SrRNA PCRq at baseline (T0), 7 (T1) and 21 (T2) days after treatment.

Currently biomarkers have also been used in the diagnosis of gingivitis and inflammatory changes whose etiology is due to the presence of non-removable orthodontic devices.^[3]^ Inflammatory cytokines from crevicular fluid and saliva have been evaluated, the evaluation of IL-6, IL-1β, IL-8, TNF-α and IL-10 cytokines in the unstimulated saliva and crevicular fluid by ELISA will be performed at baseline (T0), 7 (T1) and 21 (T2) days after treatment; we have included cytokines with an inflammatory and regulatory profile (IL-10). For Teymouri F, 2016,^[40]^ periodontal treatment with PDT seems to significantly reduce the levels of inflammatory mediators, impacting clinical findings, especially the GI.

Considering that fixed orthodontic treatment is a predisposing factor for biofilm accumulation and consequently for gingivitis,^[38,41]^ it is necessary to introduce innovative therapies without bacterial selectivity, of which PDT is an example,^[25]^ in order to provide uninterrupted orthodontic treatment and maintain the patient's quality of life.^[39]^

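### The sample-size statement contradicts itself on type 1 error, 34 cannot be reproduced from its stated inputs, and it sizes a secondary variable

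*Protocol article*

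**What the plan says.** Section 2.1 gives the only size justification: "To achieve an effect size = 0.40 between two groups (conventional treatment and PDT), for the difference in the amount of bacteria" found in crevicular fluid. It continues "assuming a type 1 error of 0.2" and, in the same sentence, "95% confidence level, the total sample size will be 34". It names an Excel calculation and a cited formula. It gives no power, no SD and no sidedness, and does not say what kind of effect size 0.40 is. Sections 2.5 and 2.10 make the allocation 1:1 with 17 per group. Three extra per group are added for an expected 20% dropout.

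Section 2.15 plans a Student t test, or a Mann-Whitney test if the data are not normal, on completers only: "Data will be presented by their means ± SD and the p value will be set at 0.05".

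Section 2.13 names GI at baseline, 7 and 21 days as the primary variable and puts the bacterial count among the secondary variables. The Discussion agrees: "The GI was defined for this study as a primary variable".

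**The concern.** Three things in or around one sentence do not fit together.

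- **Error rate.** A 95% confidence level means a type 1 error of 0.05, so 0.2 cannot be the type 1 error of the same calculation, nor of the analysis in section 2.15.
- **Number.** On its usual reading, an effect size of 0.40 between two groups is modest, and 17 per group is far too few to detect it reliably.
- **Variable.** The calculation concerns a secondary variable. Correcting its arithmetic would still leave the primary comparison without a size basis.

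A reader would take section 2.1 to mean that 34 participants are adequate for an effect of 0.40. If they are not, a non-significant result says much less about the adjunctive effect of PDT than the protocol implies.

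**Working it through.** **Inputs.** From the article: effect size 0.40, two groups 1:1, 17 per group, 95% confidence, 0.2 labelled as type 1 error (all 2.1 and 2.10); significance level 0.05 and a two-group t test (2.15). Assumed, because not stated: 80% power (reading 0.2 as the type 2 error) and two-sided testing. Other readings are tried below.

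**Step 1: try to reproduce 17 per group with 0.40 as a standardised difference d.**

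n per group = 2(z₁₋α/₂ + z₁₋β)² / d² = 2(1.960 + 0.842)² / 0.40² = 98.1, so 99 by the normal approximation. The exact t calculation gives 100. The stated figure is 17, so it is not reproduced.

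**Step 2: other readings.** Exact t; n is for 80% power.

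| Reading of 0.40 | Type 1 error | n per group needed | Power at 17 per group |
|---|---|---|---|
| d = 0.40 | 0.05 two-sided | 100 | 20.5% |
| d = 0.40 | 0.05 one-sided | 78 | 30.7% |
| d = 0.40 | 0.20 two-sided | 57 | 45.6% |
| d = 0.40 | 0.20 one-sided | 36 | 62.5% |
| Cohen's f = 0.40 (d = 0.80) | 0.05 two-sided | 26 | 61.9% |
| Cohen's f = 0.40 (d = 0.80) | 0.20 two-sided | 15 | 84.6% |

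None gives 17. Taking 0.2 literally as the type 1 error does not rescue the figure. Only the last row has 80% power at 17, and its type 1 error conflicts with the 95% confidence level and with section 2.15.

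**Step 3: 0.40 as a raw difference.** The standardised difference detectable with 17 per group (two-sided 0.05, 80% power) is (1.960 + 0.842) × √(2/17) = 0.961 by the normal approximation, or 0.991 by exact t. A raw difference of 0.40 would therefore need an SD of 0.40/0.961 = 0.416 (0.404 by exact t). No SD is given, so this reading can be neither confirmed nor excluded.

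**Step 4: what the planned numbers detect.** With 17 completers per group, d is about 0.99 at 80% power. Recruitment is 17 + 3 = 20 per group, and 20% dropout leaves 20 × 0.8 = 16. With 16 per group the detectable d is about 1.02.

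**Step 5: sizing variable against primary variable.** Section 2.1 sizes on bacteria in crevicular fluid. Section 2.13 lists that count as secondary and GI as primary. No effect size, SD or detectable difference is given for GI anywhere in the article.

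**The case against.** The strongest reply is that the 20% figure is conditional. Section 2.1 does not say that 0.40 is a standardised mean difference, and it gives no SD, power or sidedness. The article is condensed and the full calculation may hold these inputs. A raw difference with an SD of about 0.42 would give 17 per group. A repeated-measures between-group test with f = 0.40, two visits and a correlation of 0.3 would give 34 in total.

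Much of this stands. A reader might infer that the trial has been shown to have only a one-in-five chance of success, that 0.2 must be the type 2 error, or that no reading could yield 17. The documents support none of these. Power at 17 runs from about 20% to about 62% over the readings that use a 0.05 two-sided level, depending on what 0.40 is. The type 2 reading is natural but inferred, because power is never stated. The raw-difference route stays open.

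The reply does not remove the point. The repeated-measures route needs a correlation the article does not give and is not the analysis planned in section 2.15. No unseen input can reconcile a type 1 error of 0.2 with 95% confidence in one sentence. None of these routes makes a bacterial-count calculation a justification for GI.

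It is also fair to say that stating a detectable GI difference does not show that such a difference is plausible. It only reports what the chosen size can do.

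**Conclusion.** The point holds as an inconsistency and a failure to reproduce, not as proof of one particular power.

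- The type 1 error of 0.2 is wrong as written, with no assumption needed.
- The total of 34 does not follow from the stated inputs. If 0.40 is a standardised difference, the shortfall is about sixfold (100 against 17 per group) and power is about 20%. If it is Cohen's f, the requirement is 26 per group and power is about 62%. Both assume two-sided 0.05 and a target of 80%.
- The sizing variable is secondary and the primary variable has no size basis. This also needs no assumption.

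This should be corrected because it is the sole justification given for the size of the trial.

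**What to change.** Keep the number of participants and rewrite section 2.1:

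1. State a two-sided type 1 error of 0.05, and a type 2 error of 0.20 (80% power) if that is what 0.2 meant.
2. Say what 0.40 is: standardised difference, Cohen's f or raw difference. If raw, give its unit and SD and do not call it an effect size.
3. Label the bacterial calculation as being for a secondary variable.
4. For GI, at a visit the sponsor names (section 2.13 lists three and ranks none), state that 17 completers per group detect a standardised difference of about 0.99 with 80% power, or about 1.02 with the 16 per group that 20% dropout from 20 leaves. This replaces the implied adequacy for 0.40.
5. Say that a non-significant GI result will be interpreted through its confidence interval.

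The cost is protocol wording. No patients are added, but the stated capability becomes visibly less favourable.

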### Randomization

2.5

To randomly distribute the participants into the experimental groups, a 40-lot draw will be made using the Microsoft Excel program, version 2017. The distribution of groups will be identical (1: 1) for the two groups. The distribution will be done in a blocking fashion (8 groups of 5 patients). Opaque envelopes will be identified with sequential numbers (1 to 40) and there will be information about the corresponding experimental group in the order obtained in the draw. The envelopes will be sealed and will remain sealed in numerical order until the start of the periodontal treatments. The drawing and preparation of the envelopes will be performed by a person not involved in the study. Immediately prior to periodontal treatment the investigator responsible for treatment will open 1 envelope (without changing the numerical sequence) and perform the indicated procedure. Three additional patients will be included in each group in view of the dropout predicted in any clinical study (considering a dropout of 20%).

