### Experimental design

2.10

Immediately prior to periodontal treatment, the investigator will remove and open 1 envelope (without changing the numerical sequence of the other envelopes) and perform the indicated procedure. In this manner, the 34 patients will be allocated into the experimental or control groups, as follows:

**G1**- Control group (n = 17) - patients will receive scaling and oral hygiene guidance + application of placebo PDT.

**G2**- Experimental group (n = 17) - patients will be treated with scaling and oral hygiene guidance + PDT application. Photodynamic therapy will be performed at 8 sites with gingival hyperplasia (pseudopocket).

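### Three extra participants per group cover a 15% drop-out, not the stated 20%: 20 per group less 20% leaves 16, one short of the calculated 17

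*Protocol article*

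**What the plan says.** Section 2.1 (Calculation of sample size) gives the result of the calculation: "the total sample size will be 34 participantsdistributed into 2 groups". It then sets the allowance: "Considering a 20% drop-out, 3 extra participantswill be inserted into each group". That sentence goes on to mention a final sample per group, but no number stands there in the text available.

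Section 2.5 (Randomization) repeats the allowance: "Three additional patients will be included in each group in view of the dropout predicted in any clinical study (considering a dropout of 20" per cent). It also fixes how many are randomised: "a 40-lot draw will be made using the Microsoft Excel program", with equal allocation: "The distribution of groups will be identical (1: 1) for the two groups". That is 20 per group.

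Section 2.10 (Experimental design) describes the opening of those envelopes and says: "In this manner, the 34 patients will be allocated into the experimental or control groups", with 17 in each arm. The abstract likewise has the study including 34 patients, 17 per group.

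Section 2.15 (Statistical analysis) restricts the analysis to participants who complete the study. Sections 2.3 and 2.11 add to the losses after enrolment: starting a prohibited medicine or using a mouthwash, for example, takes a participant out.

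**The concern.** A drop-out allowance should leave the calculated number once the assumed fraction has been lost. Here 3 are added to 17 and the result is described as covering 20%, but 20% of 20 is 4. Because only completers are analysed, every loss reduces the analysed sample directly, so the plan falls short of its own calculated size at its own drop-out rate.

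There is a second, separate inconsistency. The same envelopes are said to allocate 34 participants in one section and are prepared for 40 in another. A reader who later judges attrition needs one number randomised and one number that the calculation required. The document does not keep the two apart.

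**Working it through.** **Inputs**
- Calculated total before the allowance: 34 (section 2.1), 17 per group (section 2.10).
- Assumed drop-out: 20%; allowance: 3 per group (sections 2.1 and 2.5).
- Lots drawn: 40, allocation 1:1 (section 2.5).
- Analysis set: completers only (section 2.15).
- Effect size: 0.40 (section 2.1), read here as a standardised mean difference. This reading is an assumption.

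**Step 1: reproduce the plan's own number.** 17 + 3 = 20 per group and 2 × 20 = 40, which matches the 40 lots. The 3 appears to come from 20% of 17: 0.20 × 17 = 3.4, rounded down. The document does not show this step.

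**Step 2: apply the stated drop-out.** Completers = randomised × (1 − drop-out).
- Per group: 20 × 0.80 = 16, against 17.
- In total: 40 × 0.80 = 32, against 34.

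**Step 3: drop-out that the allowance does cover.** 3/20 = 15%.

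**Step 4: number that would keep 17 at 20%.** Randomised = target/(1 − drop-out) = 17/0.80 = 21.25, rounded up to 22 per group (44 in total). With 21 per group, 21 × 0.80 = 16.8, still below 17; with 22, 22 × 0.80 = 17.6.

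**Step 5: how often 17 would be reached.** Assume that participants drop out independently with probability 0.20.

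| Randomised per group | Expected completers | Chance that a group keeps at least 17 |
|---|---|---|
| 20 | 16.0 | 0.41 |
| 22 | 17.6 | 0.73 |

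With 20 per group, both groups keep at least 17 with probability 0.41 × 0.41 = 0.17.

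**Step 6: effect on power.** Two-sample t-test, two-sided 0.05. Section 2.1 gives 0.2 as the type 1 error beside a 95% confidence level; I read these as 80% power and alpha 0.05, which is an assumption.

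| Completers per group | Power at a standardised difference of 0.40 | Difference detectable with 80% power |
|---|---|---|
| 17 | 20.5% | 0.99 |
| 16 | 19.5% | 1.02 |

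**Step 7: the number randomised, side by side.**
- Section 2.5: 40 lots, 20 per group.
- Section 2.10: 34 allocated, 17 per group.
- Abstract: 34 included, 17 per group.

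Thirty-four is the calculated number before the allowance. It is not the number of envelopes, and it is not what remains of 40 after a 20% loss.

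**The case against.** **The document may not promise 17 completers.** The figure after drop-out is absent from the available text of section 2.1. A reader might infer that the protocol expressly states 17 per group after drop-out and contradicts itself there. The text does not support that: section 2.10 gives 17 as the number allocated, and the missing figure could even be 16, in which case that sentence would agree with itself. This part of the objection stands, so 17 as the completer target is an inference. It is a well-founded one, because 34 is the result of the calculation and an allowance added on top of it is meant to preserve it. Nor can the 17 already contain the allowance, since 17 + 3 = 20 matches the 40 lots.

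**The cause is not documented.** Rounding 3.4 down to 3 is a plausible explanation, not a stated one. The shortfall does not depend on it.

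**Section 2.10 is not a further instance of the same error.** A reader might count sections 2.1, 2.5 and 2.10 as three wrong drop-out statements. Sections 2.1 and 2.5 state one allowance twice, and 2.10 contains no drop-out figure. Its 34 can be read as the base number, with six more added under 2.5. It remains at odds with the 40 lots as a count of those allocated, but that is a different point, and the abstract shares it.

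**The effect is slight.** One participant per group and one percentage point of power change no test, endpoint or allocation rule. This is right and limits the weight of the point. It does not make the 20% statement correct.

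**Conclusion.** The point holds as a minor correction. The allowance of 3 per group covers a 15% drop-out. At the stated 20%, 16 per group (32 in total) remain, against the calculated 17 (34), and keeping 17 would take 22 per group. This rests on the completers-only analysis, on equal drop-out in the two groups, and on reading 17 as the number that the allowance was meant to protect. Separately, the number randomised is inconsistent: 40 in section 2.5, 34 in section 2.10 and in the abstract.

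Two stronger readings should be avoided. The shortfall does not by itself compromise the trial: power at a standardised difference of 0.40 moves only from 20.5% to 19.5%. Nor does treating 17 as the reference confirm it as adequate. The same figures show power of about one in five at the stated effect size if that is a standardised mean difference. How 34 was derived is a separate question, and if it is recalculated the allowance must be recalculated with it.

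**What to change.** No extra participants are needed for this point.

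- **Sections 2.1 and 2.5:** state that 40 are randomised (20 per group), which leaves 17 per group if drop-out is at most 15% and 16 per group at 20%. Supply the figure missing from the last part of the drop-out sentence in 2.1, if it is also missing from the source.
- **Section 2.10 and the abstract:** give 40 (20 per group) as the number randomised, and describe 34 (17 per group) as the calculated number before the drop-out allowance. Do not describe 17 as sufficient for the stated effect size.

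The cost is a few sentences in four places. If the sponsor prefers to keep the 20% claim with 17 completers per group, the number randomised becomes 22 per group, which is 44 in total and four more than the 40 envelopes planned.
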